## Background

Approximately 2.5 million people around the world suffer from multiple sclerosis (MS) [1], a chronic inflammatory disorder of the central nervous system (CNS). Inflammation, demyelination, and axonal degeneration are distinctive features of the pathological mechanism [2]. Its clinical course is typically characterized by initial episodes of transient neurological deficits with full or partial recovery (relapsing-remitting MS); over the time deficits may cumulate to increasing disability. With the development of new therapeutic agents treatment goals are changing from solely stabilizing to reversing the disease.

Alemtuzumab is a new promising therapy for RRMS, which might be able to fulfil this aim. Alemtuzumab has been approved by the EMA (European Medicines Agency) in September 2013 and the FDA (U.S. Food and Drug Administration) in November 2014 for the treatment of RRMS under the name Lemtrada®. It is a humanized monoclonal antibody targeting CD52 primarily expressed on T- and B-lymphocytes, and to lesser extents on dendritic cells, monocytes and macrophages [3]. Alemtuzumab leads to a rapid and significant depletion of CD52 expressing cells by antibody-dependent cell-mediated and complement-dependent cytotoxicity [4, 5]; hematopoietic precursor cells are not affected. Subsequent to depletion a slow repopulation starts arising from hematopoietic precursor cells following a distinct pattern. B cells repopulate rapidly within 6 months with predominating immature B cells, prolonged CD27^+^ memory B cell lymphopenia and increased serum levels of BAFF (B cell activating factor) [6]. In contrast, CD4^+^ and CD8^+^ lymphocytes do not recover to the lower limit of normal (LLN) before 35 or 20 months respectively post treatment [7]. CD4^+^ memory cells predominate in the CD4^+^ cell population probably based on homeostatic proliferation of cells that escaped depletion. Similarly, CD4^+^CD25^high^CD127^dim/-^ regulatory T cells (Treg) are found to be relatively upregulated 9 months after alemtuzumab treatment [7, 8]. In contrast, the proportion of proinflammatory cell-types such as T helper (T_h_) 1 and T_h_ 17 cells and the serum levels of their respective cytokines are reduced [9]. The reduced levels of circulating B and T cells after alemtuzumab treatment accompanied by successive repopulation restoring immune tolerance networks are assumed to underlie its strong anti-inflammatory effects in multiple sclerosis.

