## Methods/design

### Study design

ALAIN01 is a single center, single arm, explorative phase IV study to elucidate further insights into the MOA of alemtuzumab treatment in 15 patients with RRMS. The study center is the Department of Neurology at the University Hospital Münster, Germany. Recruitment started in May 2015.

After a screening period of at most 28 days, eligible patients will start investigational treatment. The study is designed for 3 years and efficacy and safety measures are assessed on at least half-yearly visits. Additionally, blood and urine samples will be collected monthly to monitor for autoimmune diseases, which may be carried out by a local physician.

As required by the summary of product characteristics (SmPC) for Lemtrada®, patients will be advised to continue monitoring for late undesirable effects of Lemtrada® after termination of study participation. The study site will provide post-study patient care but also support continuation of medical attendance by a resident neurologist of the patient’s choice.

The clinical study is registered at clinicaltrials.gov (NCT02419378). It will be performed in accordance with the approval of the local ethics committee (Ethik-Kommission der Ärztekammer Westfalen-Lippe und der Westfälischen Wilhelms-Universität Münster, 2014-545-f-A), the requirements of the current German drug law (“Arzneimittelgesetz”), the current legal provisions regarding data protection, and the principals of Good Clinical Practice.

All participants are obliged to hand in the signed informed consent form (ICF).

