### Patient population and selection

Patients with highly active RRMS will be included in the study. The below eligibility criteria imply, that they are indicated to receive alemtuzumab irrespective of study participation.

Patients who do not meet all the inclusion criteria in Table 1 or meet one of the exclusion criteria mentioned in Table 2 will be excluded from further study participation. Patients will also be excluded if treatment with alemtuzumab has not been started within 28 days after signing the informed consent form. Reasons for exclusion will be recorded in the CRF. Excluded patients may be re-screened at a later time.

**Table 1 Tab1:** Inclusion Criteria

Patients must meet all of the following criteria to be eligible for further study participation:	
1. Signed informed consent form (ICF)	
2. Age 18 to 55 years old (inclusive) as of the date the ICF is signed	
3. Diagnosis of MS according to the McDonald criteria 2010 and cranial MRI scan demonstrating white matter lesions attributable to MS within 10 years before screening	
4. Onset of MS symptoms (as determined by a neurologist, either at present or retrospectively) within 10 years of the date the ICF is signed	
5. EDSS score 0.0 to 5.0 (inclusive) at Screening	
6. Patients with (highly) active RRMS disease course indicated to receive alemtuzumab according to the following conditions (at least 1 out of 3 conditions has to be fulfilled):	
1. ≥2 MS relapses within 24 months	
2. Clinical (≥1 relapse) or MRI (new gadolinium enhancing lesions) disease activity under therapy with other disease-modifying therapies	
3. Severe relapse with high disease activity (≥9 T2 hyperintense Lesions and ≥1 gadolinium enhancing lesion) on MRI.	
7. Completion of all vaccinations required by the applicable immunization guidelines published by “ständige Impfkommission” (STIKO)	
8. History of chickenpox or positive test for antibodies against varizella zoster virus (VZV)

**Table 2 Tab2:** Exclusion Criteria

Patients will be excluded from this study if they meet any of the following exclusion criteria:	
1. Participation in another clinical trial at present or within 4 weeks of study entry. There may be exceptions at the discretion of the Investigator.	
2. Has any progressive form of MS	
3. Hypersensitivity to the active substance, or to any of the excipients of Lemtrada®	

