##### Multi-electrode Array

To analyse the impact of cell culture supernatants or cerebrospinal fluid on activity of neuronal networks, different parameters of neuronal network activity will be determined using the multi-electrode array technique [36–38]. Multi-electrode array detects compound field potentials in the spatial vicinity of multiple extracellular electrodes in densely cultured hippocampal neurons, which are capable of generating spontaneous synchronized activity. A complete listing is found in Table 5.

**Table 5 Tab5:** Additional Endpoints

The following additional endpoints will undergo exploratory evaluation:	
1. Number of patients who experienced sustained accumulation of disability (SAD) during the study period (Study period: From the day of treatment initiation until month 36 visit. SAD: for patients with a Baseline EDSS score of 0.0, SAD is defined as an increase of ≥1.5 points sustained over a 6-month consecutive period. For patients with a Baseline EDSS score of ≥1.0, SAD is defined as an increase of ≥1.0 point sustained over a 6-month consecutive period.)	
2. Time to SAD	
3. Time to sustained reduction in disability (SRD) based on EDSS scores (SRD: a ≥1 point decrease on the EDSS sustained for 6 consecutive months for patients with a baseline EDSS ≥2)	
4. Absolute Number of relapses during the study period	
5. Number or relapses which occurred during the study period and required corticosteroid therapy	
6. Proportion of patients who are relapse free at year 3	
7. Time to first relapse	
8. Absolute and relative change from baseline in the following functional scores at each time point of assessment after treatment initiation (see Additional file 1: Assessment Schedule): EDSS, visual functional system score as part of the assessments for EDSS, MSFC and each MSFC component, FSMC and each subscore (mental and physical fatigue)	
9. The proportion of patients who have worsened, remained stable, or improved as indicated by change from Baseline in EDSS scores at the end of the study	
10. Change from baseline of the following HRQoL measures at each time point of assessment after treatment initiation (see Additional file 1: Assessment Schedule): FAMS, EQ-5D (total score, Physical Component summary Measure, Mental Component Summary Measure), SF-36	
11. The proportion of patients who have worsened, remained stable, or improved as indicated by change from Baseline in MSFC scores at the end of the study	

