12. Absolute and relative change from baseline amplitudes [V] and latencies [s] of evoked potentials (VEP, SEP, MEP)	
13. Percent change from baseline in magnetic resonance imaging (MRI)-T2 hyperintense lesion volume at each time point of assessment after treatment initiation (see Additional file 1: Assessment Schedule)	
14. Number of new gadolinium-enhancing lesions on MRI-T1 in comparison to Baseline	
15. Number of new or enlarging hyperintense lesions measured by T2-weighted MRI in comparison to Baseline at each time point of assessment (see Additional file 1: Assessment Schedule)	
16. Absolute and relative change from baseline of IL-21 concentration in blood serum at indicated time-points of sampling	
17. Absolute and relative change from baseline of following parameters assessed in CSF: cell counts, concentration of lactate, protein, and immunoglobulines (IgA, IgG, IgM)	
18. Qualitative assessment of the change in presence of oligoclonal bands in CSF from baseline	
19. Proportion of patients with no MS disease activity (i.e., deterioration in MRI related endpoints, relapse) at the end of the study	

At our study center samples of highly controlled and validated groups of other MS therapy cohorts (e.g. natalizumab and fingolimod) and other neuroimmunological diseases (NMO, CIDP, autoimmune encephalitis) and healthy sex- and age-matched individuals are available as control groups. These control groups will be used for experiments, whenever it is possible and reasonable.

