Another focus of our study is on the migrational capacity of T cells after alemtuzumab treatment. It is assumed for MS that autoimmune T cells migrate into the CNS after they have been activated in the periphery [44–46]. A study of Havari and colleagues has recently shown that anti-murine CD52 treatment had no effect on the migratory ability of immune cells [47]. However, since results from animal experiments cannot be easily transferred these findings have to be further evaluated in humans. Moreover, CD52 has been shown to play a role in transendothelial migration of T cells through human umbilical vein endothelial cell monolayers [48].

More uncertainty surrounds the neuroprotective potential of alemtuzumab compared to anti-inflammatory effects. A post hoc subgroup analysis of the CAMMS223 trial demonstrated a significant improvement in EDSS scores even in patients without pre-treatment clinical disease activity (EDSS improvement by 0.31 points, *P* < 0.005) indicating potential neuroprotective effects of alemtuzumab [15]. In vitro experiments with peripheral blood mononuclear cells of alemtuzumab treated patients produced increased amounts of neurotrophins and were able to prolong survival of murine neurons and oligodendrocytes [15]. However, immune cells producing neurotrophins have not been detected in the CNS of alemtuzumab treated patients so far. Moreover, the short half-lives and the inability to pass the blood-brain-barrier (BBB) of neurotrophins argue against an effect of peripherally detected neurotrophic factors in the CNS [49]. Combining longitudinal clinical (SAD, SRD), MRI (brain atrophy, structural integrity) and experimental (neurotrophins and markers for neurodegeneration in the CSF, impact on neuronal networks in vitro) our study intends to evaluate potential neuroprotective properties of alemtuzumab.

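### A baseline EDSS scored in or soon after a relapse is allowed, so natural relapse recovery can count as SRD or 'improved' and raises the bar for SAD

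*Protocol article*

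**What the plan says.** All references are to the protocol article.

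- **Endpoints (Table 5).** Item 3 gives "SRD: a ≥1 point decrease on the EDSS sustained for 6 consecutive months for patients with a baseline EDSS ≥2". Item 1 defines SAD as a rise from baseline held for 6 months: at least 1.5 points if baseline is 0.0, at least 1.0 point if it is 1.0 or more. Item 8 reports EDSS change from baseline at each assessment. Item 9 classifies patients as worsened, stable or improved at study end. No item sets a condition on relapse status at baseline.
- **Entry (Table 1).** The disability criterion is "EDSS score 0.0 to 5.0 (inclusive) at Screening". One of three activity conditions must be met. The third is "Severe relapse with high disease activity (≥9 T2 hyperintense Lesions and ≥1 gadolinium enhancing lesion) on MRI". The second accepts a relapse, or new enhancing lesions, under another disease-modifying therapy. Neither sets a minimum time since the relapse.
- **Timing (Study design).** "After a screening period of at most 28 days, eligible patients will start investigational treatment".
- **Natural course (Background).** MS typically begins with "initial episodes of transient neurological deficits with full or partial recovery".
- **Control (Study design; text after Table 5).** "ALAIN01 is a single center, single arm, explorative phase IV study". Of the stored samples from other cohorts it says "These control groups will be used for experiments, whenever it is possible and reasonable". It does not name these cohorts as comparators for EDSS.
- **Use (Discussion).** The neuroprotection question is to be addressed by "Combining longitudinal clinical (SAD, SRD), MRI (brain atrophy, structural integrity) and experimental" data.

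**The concern.** A patient may be scored while a relapse deficit is still present and be treated within four weeks. If the deficit then resolves, as the Background says relapse deficits fully or partly do, the fall in EDSS meets the stated SRD rule without any drug effect. The 6-month confirmation does not screen this out, because completed recovery is itself sustained. The raised baseline also makes SAD harder to reach. Both errors flatter the treatment, and there is no concurrent clinical control to show how much of the change is natural recovery.

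What is at stake is the clinical part of the neuroprotection evaluation. The Discussion supports that question with an earlier analysis in patients without clinical disease activity before treatment, a group in which relapse recovery is a less likely explanation. This trial requires clinical or MRI activity at entry and does not carry that separation over.

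**Working it through.** **Plan's own figure.** The article gives no numerical planning for EDSS. Its only planning figures are the lymphocyte confidence-interval half-widths under Sample size. With t(0.975, n−1) × SD × √(χ²(0.80, n−1)/(n−1)) / √n, they recompute as 283.7/375.4, 31.5/41.7 and 315.3/417.2, against the stated 284/375, 32/42 and 315/417. They reproduce and do not bear on this point.

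**Step 1: can a relapse-time baseline occur?** Tables 1 and 2 contain no relapse-free interval. The nearest safeguard is exclusion 30, which bars antineoplastic or immunosuppressive drugs within 8 weeks of inclusion. It names neither relapses nor corticosteroids. If corticosteroids count, some steroid-treated relapses are removed, but untreated relapses still pass. So such a baseline is permitted.

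**Step 2: apply the Table 5 thresholds.** SRD requires baseline ≥2 and a fall ≥1.0. SAD for baseline ≥1.0 requires baseline + 1.0.

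| Stable EDSS | Baseline in relapse | Fall on full recovery | SRD met? | EDSS needed for SAD | Rise from stable level |
|---|---|---|---|---|---|
| 1.0 | 2.5 | 1.5 | yes | 3.5 | 2.5 |
| 2.0 | 3.0 | 1.0 | yes | 4.0 | 2.0 |
| 2.0 | 3.5 | 1.5 | yes | 4.5 | 2.5 |
| 3.0 | 5.0 | 2.0 | yes | 6.0 | 3.0 |

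From a relapse-free baseline, each of these patients would need a rise of only 1.0 for SAD. For the patient stable at 2.0 that means 3.0 rather than 4.5, and return to 2.0 would give no SRD. In the first row the relapse alone brings the patient into the SRD set. A later lasting return to 2.5 would be no change from baseline, although it is 1.5 above the stable level. Partial recovery can also qualify: 3.5 to 2.5 is a fall of 1.0 and leaves the patient 0.5 above the stable level.

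**Step 3: how many events?** The article gives none of the shares needed, so all three are assumptions:

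- f: share of patients with a baseline in or soon after a relapse that raised EDSS by at least 1;
- h: share of those with baseline EDSS ≥2;
- g: share of those with a lasting recovery of at least 1 point.

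Expected recovery-only SRD events = 15 × f × h × g.

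- f = 0.20, h = 1, g = 0.50: 15 × 0.20 × 0.50 = 1.5 (1.5/15 = 10%).
- f = 0.40, h = 1, g = 0.60: 15 × 0.40 × 0.60 = 3.6 (3.6/15 = 24%).
- h = 1 treats every such patient as eligible for SRD. With h = 0.5 the two results halve to 0.75 and 1.8. With f = 0 there are none.

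The chance of at least one such event is 1 − (1 − fhg)^15. With g = 0.50:

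- fh = 0.10: 0.54
- fh = 0.20: 0.79
- fh = 0.33: 0.93

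**Step 4: mean EDSS change (item 8).** If a share f recovers d points and the others do not change, the mean shifts by −f × d. This runs from −0.10 (f = 0.10, d = 1) to −0.66 (f = 0.33, d = 2). For scale only, the article reports gains of 0.39 (Background) and 0.31 (Discussion) from an earlier trial.

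**The case against.** The strongest reply has five parts.

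- **The article is condensed.** The assessment schedule, the full protocol and the SAD criteria of the earlier trial that the article relies on are not shown, and one of them may define baseline more tightly. This limits confidence. It does not remove the point, because Table 5 spells out thresholds, confirmation period and baseline subset, Tables 1 and 2 are presented as the operative criteria, and none contains a relapse condition.
- **Nothing shows that patients are screened in relapse.** The first activity condition allows relapses up to 24 months back, the second can be met on MRI alone, and the third gives no date for the severe relapse. Exclusion 30 may remove some cases. This stands: the criteria permit the problem, but its frequency is unknown.
- **The event counts are assumed.** This also stands. The 1.5 to 3.6 range ignores the baseline ≥2 condition. Nor can it be set against the 41% SRD quoted in the Background, which uses a different definition and 4 years of follow-up.
- **A reader might infer that later worsening is hidden.** The documents do not support that. Item 8 would show a fall followed by a rise, and relapses are counted separately. The masking is confined to the SAD count and the end-of-study category in item 9.
- **A reader might infer that the trial will read SRD as neuroprotection.** The Discussion says only that potential neuroprotection will be evaluated, and it combines SAD and SRD with MRI and experimental measures. These are additional endpoints, inference is declared exploratory, and the article concedes that the number of patients limits definite conclusions.

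**Conclusion.** The point holds as a weakness in how exploratory disability endpoints are anchored. Followed as written, the Table 5 rules can count natural relapse recovery as SRD or as 'improved', and they raise the level at which SAD is declared. The threshold arithmetic follows directly from the article. The number of patients affected does not: 1.5 to 3.6 events in 15 is an upper-end illustration under assumed shares, and the true figure could be close to none. With so few patients, one or two such events would still visibly change the SRD result.

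The stronger conclusion, that the trial's findings or its neuroprotection evaluation as a whole are invalid, is not supported. The primary immune-cell endpoints are unaffected, and the MRI and laboratory parts of the neuroprotection question do not use the baseline EDSS. Under-counting of SAD is possible, not certain.

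**What to change.** - Record the onset date of the last relapse before the baseline EDSS.
- Specify, before analysis, an interval from relapse onset within which a baseline EDSS counts as relapse-affected. The article gives no basis for a particular length, so the trial team should choose and justify it.
- Report SAD, SRD and item 9 for all patients, and again without patients whose baseline EDSS fell within that interval.
- Base the clinical part of any neuroprotection statement on the second analysis.

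Do not replace the baseline with another EDSS. A post-treatment reference would absorb any early treatment effect. With half-yearly visits, and disability assessed at least annually, it could fall 6 to 12 months after dosing. A pre-relapse reference could turn incomplete recovery from a pre-treatment relapse into an on-treatment SAD. Mixing kinds of reference in 15 patients would also harm comparability.

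The cost is one more recorded date and a smaller set for the second analysis, which remains uncontrolled. Eligibility and treatment timing do not change.

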### Additional endpoints

Additional endpoints include clinical parameters, a number of extensive clinical scales as well as instrument-based diagnostics and are listed in detail in Table 5.

Patient disability will be evaluated at least at annual visits as specified in the Additional file 1: Assessment Schedule using EDSS as well as the specific criteria for SAD on the basis of the CAMMS223 study [14] accompanied by clinical outcome measurements applying the Multiple sclerosis functional composite (MSFC) and fatigue evaluation by the Fatigue Scale for Motor and Cognitive Functions (FSMC). The Health-Related Quality of Life (HRQoL) will be assessed by three self-report measures, the Functional Assessment of Multiple Sclerosis (FAMS), the EuroQol (EQ-5D) and the Short Form-36 (SF-36).

Instrument-based diagnostics encompass evoked potentials, optical coherence tomography and MRI scans including the rate of gadolinium-enhancing MRI lesions, total MRI-T2 lesion volume plus photon density and fluid attenuated inversion recovery (FLAIR) sequences as well as 3D-T1 and DTI acquisitions.

These investigations will be completed by measurements of serum concentrations of IL-21 at indicated time points (see Additional file 1: Assessment Schedule) by appropriate ELISA kits according to manufacturer’s instructions. Increased IL-21 concentrations in the serum have been associated with a higher risk for the development of secondary autoimmunity under alemtuzumab therapy. IL-21 is assumed to drive cycles of T cell expansion and apoptosis to excess leading to higher stochastic opportunities for T cells to encounter self-antigens, and hence autoimmune reactions. Therefore IL-21 might be used as a biomarker for the risk of developing autoimmunity providing essential information for clinical decisions [39].

### Sample size

Concerning the prevalence and the inclusion and exclusion criteria of this study, it seems feasible to recruit 15 patients over the course of 1 year. The absolute number of lymphocytes before and after treatment with alemtuzumab as described in previous studies [6, 8, 29] was used to assess the expected precision of the mean absolute number of cells estimation that can be attained with this number of patients:

The absolute number of lymphocyte cells before treatment is assumed to be 2100 ± 450 cells/μl (mean ± standard deviation). With a probability of 80 % a 95 % confidence interval for the mean number of lymphocyte cells measured in 15 patients before treatment would not exceed a range of ±284 cells/μl. With a probability of 80 % the 95 % confidence interval would not exceed a range of ±375 cells/μl in case samples of only 10 patients can be collected.

The absolute number of lymphocyte cells after treatment is expected to be lowered to 100 ± 50 cells/μl. With a probability of 80 % a 95 % confidence interval for the mean number of lymphocyte cells measured in 15 patients after treatment would not excess a length of ±32 cells/μl. With a probability of 80 % the 95 % confidence interval would not excess a length of ±42 cells/μl in case samples of only 10 patients can be collected.

The difference in absolute numbers of lymphocyte cells before and after treatment is assumed to be 2000 ± 500 cells/μl. With a probability of 80 % a 95 % confidence interval for the mean change in number of lymphocyte cells measured in 15 patients would not excess a length of ±315 cells/μl. With a probability of 80 % the 95 % confidence interval would not excess a length of ±417 cells/μl in case samples of only 10 patients can be collected.

The precision of this estimation is considered to be sufficient to track the condition of the immune system over time to describe the MOA of alemtuzumab treatment.

These calculations were performed using NQuery Advisor® 7.0.

